#### User-centric considerations in the health recommender system

Based on Wendel et al.’s study [47] on fostering health recommendation systems, we took into account the following:Effort: Any effort required from the patient’s side has been minimized by removing the entry barrier of having to manually input their profile details. These details are automatically loaded from the hospital electronic health record.Privacy risk: The app only stores the patient’s name and all communication follows the MD5 encryption protocol as required to meet the hospital’s privacy requirements. The app and the electronic health record exchange XML documents following the HL7 protocol using the Mirth Connect engine.Usefulness: The topics of the messages and the messages themselves were validated by a psychologist and pulmonologist to make sure they contain relevant scientific information.Enjoyment: The use of friendly and familiar language combined with the frequency and timing of the messages makes the app feel personal and less robotic. This follows the gamification principle of “unpredictability and randomness” as per the Octalysis gamification framework [63].

Finally, Wendel et al.’s study also referred to the intermediary that introduces the system to the patients. In this case, it is the healthcare professional from the hospital’s smoking cessation unit who presents and endorses the m-HRS. This fact may also positively contribute to patients using it.

#### Choosing the message topic

The data on the message ratings and the patients’ interaction with the app will be sent to the hospital server, where it will be processed by an HRSA to enable it to choose the next message for each user as well as the time at which it should be sent. Figure 3 shows a conceptualization of this mHealth Recommender System architecture. The HRSA is an algorithm that follows a hybrid approach to improve its performance, as suggested by Burke [64]. The algorithm combines the following three factors to compute the results:Patient’s demographic similarity: Demographic influence will be based on the similarity of patients in terms of their age, gender, employment status, date they stopped smoking, and scores on the Fagerström [65] and Richmond tests [66].Perceived utility of the message topics: The utility of the messages will be measured as follows: Patients will be prompted to rate each message with “like”, “dislike”, or “neutral”. In case of multiple ratings given to the same message, the old ratings will be overridden. Visits to sections of the app on the same topic as the messages or re-read messages on a given topic will also be considered.Statement of initial interest: Patients need to fill out a questionnaire consisting of five questions in which they state their interest in the five message topics. This interest can be rated as positive, neutral, or negative. Patients can modify their answers anytime through the app.

**Fig. 3 Fig3:**
[figure not shown]
Description of the mHealth Recommender System’s architecture and flow of data information

Once the topic has been selected, the system selects a previously unsent message from the database and tailors it to the user so that it is more personalized. For instance, the message may include the name of the user.

#### Sending the messages

The frequency at which patients will receive messages is based on the conclusions of Abroms et al. [67] considered in combination with the transtheoretical behavior change model [68]. This model was chosen because the counseling offered at the hospital’s smoking cessation unit is partially based on it, and we wanted the messages to be in line with this counseling. We started considering patients in the preparation phase, which is when they can join the program.Preparation: One message a day until the day of quitting—the topic of these messages is not predicted by the HRSA but chosen at random, and they cannot be rated, so they have no influence on the HRSAAction: Four messages on the day of quitting, and one message a day for the following week.Maintenance: Three messages a week after that, for one year.

In the maintenance phase, as per the transtheoretical behavioral change model, the messages will be sent at random days during the week. In total, a patient who completes the yearlong treatment will receive a total of 150 messages from the m-HRS. The time at which the messages will be sent is also calculated by the HRSA, based on the time difference between when a message is sent and when it is read. The day will be divided in 12 two-hour periods during which the message can be sent at any random time. The sooner the patient reads the message after receipt, the more likely it is that the next message will be sent in the same two-hour period. Patients can deactivate messages during a specific period of time through a do-not-disturb setting. Just like the final decision of the message topic, the messages’ timing is also based on a probability vector.

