### Quality

#### Objective quality

Since the HRSA predicts the message topic and timing of delivery, the objective perceived quality will be measured using two metrics: the precision of the message topics, and how long after receiving the message the users read it.

The precision metric is defined as the relation between the number of hits per message in the first month (baseline) and the extent of “positive”, “neutral”, and “negative” feedback per message in month 3, month 6, month 9, and month 12. Hits are messages with only positive feedback (1) Precision_p_ and with both positive and neutral feedback (2) Precision_p&n_.

1$$ Precisio{n}_P=\frac{\mid \mathrm{m} essages\ with\ positive\ feedback\mid }{\mid all\  messages\ with\  any\  feedback\mid } $$
2$$ Precisio{n}_{p\&n}=\frac{\mid messages\ with\ positive\ and\ neutral\ feedback\mid }{\mid all\  messages\ with\  any\  feedback\mid } $$

We expect the acceptance rate to be higher in month 12, as compared to the previous months, as by this time the HRSA will have more patients and enough information to make accurate decisions.

We will calculate the precision of the system at different points of time, which will reflect the users’ feedback and their interactions with specific sections of the app. All this information is stored in the database of the m-HRS.

The time-to-read metric is defined as the time difference between when the message was sent and when it was read by the user. We will use it to assess the evolution in the quality of the HRSA to predict the best time at which to send a user messages—we theorize that the lesser the time-to-read, the better it is for the user to receive messages at that time.

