## Discussion

This study will explore how patients enrolled in a smoking cessation program perceive and engage with an m-HRS that sends them periodic motivational messages encouraging them to stop smoking. We also expect the m-HRS to help increase the low attrition rate that is typically seen in eHealth trials [74].

The answers to this study’s research questions will benefit future recommender system-based behavioral change interventions. Researchers will be able to re-use our proposed perceived quality and engagement metrics and exploit the knowledge derived in order to design new and improved health recommender systems that take into account user appreciation and engagement. Thus, the health messages sent to the users will be more interesting, relevant, and engaging for them.

We expect the patients’ perceived quality of the system to increase over time, that is, for the precision of the messages to increase and the patients’ time to read the messages to decrease. However, we should consider that, at some point during the intervention, patients may stop reading the messages because they have uninstalled the app. This may be because they have successfully quit smoking and do not want any smoking-related reminders, because they have relapsed, or because they never engaged with the app in the first place and have decided to remove it from their smartphone. Therefore, these metrics will need to be carefully analyzed to avoid simplistic conclusions.

The users’ in-app activity analytics will provide an insight into how patients react to the messages the HRSA selects for them. This opens up several future research opportunities, such as comparing whether the theoretical interests patients claim to have are in fact their interests, noting the time they stop rating messages because they are no longer interested in receiving more messages, and having an initial m-HRS-generated message patient acceptance data report for future implementation in smoking cessation programs.

However, this study may suffer from the trust problem like all recommender agents. Despite the elaborate design of the HRSA, should a patient receive a single message that is out of context, it may ruin her confidence in the system and she may stop using the m-HRS altogether [75]. In order to minimize this, the messages have been designed such that they are applicable to almost all circumstances and experiences of a patient.

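### Time-to-read is used to judge the HRSA's timing prediction, but patients can also change when messages go out, and nothing in the plan separates the two.

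*Protocol article*

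**What the plan says.** **Two controls on send time.** Under Sending the messages, the article describes the algorithm's part: "The day will be divided in 12 two-hour periods during which the message can be sent at any random time". Its timing rule favours a period again when a message sent in it was read quickly, with timing drawn from a probability vector. The same paragraph adds the patient's part: "Patients can deactivate messages during a specific period of time through a do-not-disturb setting".

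**The metric.** Under Objective quality: "The time-to-read metric is defined as the time difference between when the message was sent and when it was read by the user". Its purpose follows: "We will use it to assess the evolution in the quality of the HRSA to predict the best time". It is one of two objective quality metrics, and the only one that addresses timing. Perceived quality is a primary outcome.

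**The expectation.** The Discussion expects "the precision of the messages to increase and the patients’ time to read the messages to decrease".

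**Caveats.** The Discussion asks for careful analysis of these metrics, with reference to patients who have uninstalled the app. Limitations and generalizability mentions changing interests and the difference between working days and holidays. Neither section mentions do-not-disturb. The study is a single observational cohort, and no concurrent group with random timing is described.

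**The concern.** A change in time-to-read is informative about the HRSA only if the HRSA is what changed the send times. A patient who closes the night hours removes the slow periods personally. The metric improves, and the algorithm has done nothing.

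This is not the attrition problem that the Discussion raises. It can occur in a patient who keeps the app and reads every message.

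At stake is the conclusion on timing. The study could credit the HRSA with learning that it did not do, or, if the setting works in the other direction, miss learning that it did do. With no random-timing comparator, the two causes cannot be separated afterwards unless the setting was recorded while the study ran. The data that Objective quality names as stored are feedback and interactions with app sections; do-not-disturb is not named.

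**Working it through.** The article states no time-to-read or do-not-disturb figure, so there is nothing of its own to reproduce. The check asks whether the metric can move with the algorithm held fixed.

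**Input from the article:** 12 two-hour periods, which cover 24 hours.

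**Assumptions, not in the article:**
- Send probabilities are uniform over the periods and stay so (no learning).
- The patient sleeps from 22:00 to 06:00, which is 4 of 12 periods. A message sent then waits until 06:00.
- Once awake, the patient reads after a further mean delay of *d* hours, with *d* from 0.5 to 4.
- Do-not-disturb closes the 4 sleep periods, and blocked sends are redrawn among the other 8.

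**Step 1: one patient.** A message sent at a random moment in the 8-hour night waits 8/2 = 4 h on average.
- Without do-not-disturb: mean = (4/12) × 4 + *d* = 1.33 + *d*
- With do-not-disturb: mean = *d*

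**Step 2: the cohort.** If the share of patients using the setting rises from 0 to *x*, the proportional fall is *x* × 1.33 / (1.33 + *d*).

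| *d* (h) | Without (h) | With (h) | Fall, *x* = 25% | Fall, *x* = 50% |
|---|---|---|---|---|
| 0.5 | 1.83 | 0.50 | 18.2% | 36.4% |
| 1 | 2.33 | 1.00 | 14.3% | 28.6% |
| 2 | 3.33 | 2.00 | 10.0% | 20.0% |
| 4 | 5.33 | 4.00 | 6.3% | 12.5% |

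A simulation of 400,000 messages per setting agrees to within about 0.01 h on the means and 0.2 percentage points on the falls.

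**Step 3: constant use.** If the share is 50% in both windows, the mean is the same in both and the change is 0%. The setting then moves the level, not the trend.

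**Step 4: handling of blocked messages.** The article does not say what happens to a message that falls in a blocked period.
- Redrawn or dropped: that patient's mean falls as in step 1.
- Deferred, with the clock running from the original scheduled time: the mean need not fall.
- Still sent but silenced: the mean rises wherever the patient would otherwise have read the message sooner. The long delay also enters the timing rule, so the HRSA is steered by the setting.

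The article's wording on the clock does not settle this. Objective quality first describes the interval as starting at receipt, then defines it from sending; the two can differ when a message is held.

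**The case against.** The strongest reply is that a spurious trend needs several things the article does not state.

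- **Timing and form of the setting.** The article does not say that the setting is a recurring clock window, nor that it can be changed at any point in the year. A one-off or date-range pause would have much less effect. Messages are also sent daily in the preparation phase, so a patient bothered at night could set do-not-disturb before the quit day. Use would then be constant over the compared windows. This stands, and it makes the point conditional.
- **Direction.** This depends on implementation detail that a condensed article may leave to the full protocol. It stands too: no single direction can be claimed.
- **The outcome itself.** The primary outcome is perceived quality of the m-HRS, and do-not-disturb is arguably part of that system. Shorter waits obtained through it may count as system quality. This is fair. Only the narrower inference, from time-to-read to the HRSA's prediction, is exposed.

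A reader might go further and infer that the whole expected fall could be an artefact of the setting, or that the plan credits every change to the HRSA. The article supports neither. The first needs an algorithm that learns nothing, while the stated rule itself moves sends away from slowly read periods, which leaves do-not-disturb less to add. On the second, the article says only that the metric will be used to assess the HRSA, and it calls the link between time-to-read and good timing a theory. Nor are single-patient falls cohort figures: in the illustration, one patient who blocks the night drops by 1.33/(1.33 + *d*), or 25 to 73%, but a cohort would drop that far only if every patient did so after baseline.

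What the reply does not remove is that the metric is used to judge the HRSA while a second, patient-held control acts on the same send times, with nothing in the article to tell them apart.

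**Conclusion.** The point holds in conditional form. If do-not-disturb use changes between the compared windows, time-to-read can shift without any HRSA learning, downward or upward according to how blocked messages are handled. If use is constant from the start, the trend is not affected.

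The size cannot be taken from the article. Under the assumptions listed (uniform sending, an 8-hour night, waking delays of 0.5 to 4 h, redrawn sends, no learning), the cohort mean falls by about 6 to 18% for uptake rising from 0 to 25%, and by about 12 to 36% for uptake rising to 50%. These figures show that the effect can be material, not that it will occur. The matter should be settled because the remedy is cheap and the missing information may not be recoverable later.

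**What to change.** 1. Log each do-not-disturb setting and each change with its time. Store with each message which two-hour periods were open for that patient.
2. State what happens to a message that falls in a blocked period, and whether the clock starts at sending or at receipt.
3. Report time-to-read by do-not-disturb status alongside the crude change, and do not attribute the crude change to the HRSA alone.
4. Base the HRSA timing conclusion on a comparison, within patient and window, of observed time-to-read with that expected from random sending over the periods open at that time. In the no-learning illustration this behaves as it should: before blocking, observed and expected are both 1.33 + *d*; after blocking, both are *d*. The contrast is zero in both windows, although the crude mean has fallen.

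Do not instead restrict the analysis to periods left open throughout all windows. That conditions on later patient choices. If the HRSA had already moved sends away from the night and the patient then blocked it, a genuine gain would be deleted.

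The cost is one logged field, some more analysis, and possibly a smaller improvement credited to the HRSA. The comparison will also be noisy for a single patient: three messages a week is about 3 × 52/12 = 13 a month, spread over up to 12 periods, so the results will need to be pooled over patients.

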### Outcomes

Our primary outcomes are the patients’ perceived quality of the m-HRS and their engagement with it. We define quality as a set of features that makes the system recommend timely and relevant messages for each patient. As no formal methodology has yet been used to assess the quality of and engagement with HRS, we will use both objective and subjective quality measures along with engagement metrics at an aggregated and individual level.

### Quality

#### Objective quality

Since the HRSA predicts the message topic and timing of delivery, the objective perceived quality will be measured using two metrics: the precision of the message topics, and how long after receiving the message the users read it.

The precision metric is defined as the relation between the number of hits per message in the first month (baseline) and the extent of “positive”, “neutral”, and “negative” feedback per message in month 3, month 6, month 9, and month 12. Hits are messages with only positive feedback (1) Precision_p_ and with both positive and neutral feedback (2) Precision_p&n_.

1$$ Precisio{n}_P=\frac{\mid \mathrm{m} essages\ with\ positive\ feedback\mid }{\mid all\  messages\ with\  any\  feedback\mid } $$
2$$ Precisio{n}_{p\&n}=\frac{\mid messages\ with\ positive\ and\ neutral\ feedback\mid }{\mid all\  messages\ with\  any\  feedback\mid } $$

We expect the acceptance rate to be higher in month 12, as compared to the previous months, as by this time the HRSA will have more patients and enough information to make accurate decisions.

We will calculate the precision of the system at different points of time, which will reflect the users’ feedback and their interactions with specific sections of the app. All this information is stored in the database of the m-HRS.

The time-to-read metric is defined as the time difference between when the message was sent and when it was read by the user. We will use it to assess the evolution in the quality of the HRSA to predict the best time at which to send a user messages—we theorize that the lesser the time-to-read, the better it is for the user to receive messages at that time.

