**Discussion:**

This study will explore whether a health recommender system algorithm integrated with an electronic health record can predict which tailored motivational health messages patients would prefer and consider to be of a good quality, encouraging them to engage with the system. The outcomes of this study will help future researchers design better tailored motivational message-sending recommender systems for smoking cessation to increase patient engagement, reduce attrition, and, as a result, increase the rates of smoking cessation.

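### The two precision metrics measure acceptance of rated messages, not the HRSA's topic prediction, yet their expected rise is credited to the HRSA

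*Protocol article*

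**What the plan says.** All references are to the Protocol article.

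- **Objective quality** gives the reason for the metric, "Since the HRSA predicts the message topic and timing of delivery", and then states that "the objective perceived quality will be measured using two metrics: the precision of the message topics" is one of the two measures. The other is the time to read.
- The same section defines a hit: "Hits are messages with only positive feedback (1) Precision_p_ and with both positive and neutral feedback (2) Precision_p&n". In both formulas the denominator is every message that received a rating. The comparison is over time: "The precision metric is defined as the relation between the number of hits per message in the first month (baseline" and the feedback in months 3, 6, 9 and 12. The section expects a higher acceptance rate at month 12 because the HRSA will by then know enough to decide accurately.
- **Choosing the message topic** says the HRSA combines demographic similarity, perceived utility and stated interest. Newer ratings replace older ones, and patients may change their stated interests at any time. The text under Fig. 3 adds: "Once the topic has been selected, the system selects a previously unsent message from the database".
- **Sending the messages** says "Just like the final decision of the message topic, the messages’ timing is also based on a probability vector". It also says that preparation-phase messages have random topics and cannot be rated.
- **Abstract, Discussion** states the question: whether the algorithm "can predict which tailored motivational health messages patients would prefer". The text under Fig. 2 says the design will show whether patients prefer late messages as a result of the HRSA having been trained.

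**The concern.** The metric is introduced as a measure of the HRSA's topic prediction, but nothing the HRSA predicted enters the formulas. They count ratings. A patient who likes nearly everything gives high precision whatever topic is chosen, and a patient who likes little gives low precision even when the topic is well chosen.

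Perceived quality is one of the two primary outcomes, and precision is one of its two objective metrics. If precision rises, the article is set to credit the trained HRSA. If it stays flat, the reader cannot tell whether the HRSA failed to learn or whether patients had no topic preferences to learn. Messages with random topics, which could have served as a reference, cannot be rated. Month 1 is an earlier period, not a concurrent comparator, and its topics are not said to be random.

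**Working it through.** The article gives no target or expected value for precision, so there is no figure to reproduce. Like probabilities and topic weights below are assumptions. The five topics, the 120 patients, the 50% dropout and the three maintenance messages a week come from the article.

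**Formula.** For a patient with like probability L_k for topic k and HRSA weight w_k, with topics drawn according to the weights and all messages rated, expected Precision_P = Σ w_k L_k. AUC here is the probability that a liked message carried a higher weight than one not liked, counting ties as half.

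**1. Same level, different predictive ability.**
- No topic preference, L = 0.60 for all topics: Precision_P = 0.60 under any weights, including random choice. AUC is about 0.50.
- One favourite topic (L = 0.80, others 0.40), weights 0.50 on the favourite and 0.125 on each other: 0.50×0.80 + 0.50×0.40 = 0.60. AUC is about 0.71.

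**2. Same rise, different cause.**
- Learning in the second cohort: equal choice gives (0.80 + 4×0.40)/5 = 0.48, and the learned weights give 0.60.
- Random topics throughout, half the patients liking 28% of messages and half 68%: the start is (0.28 + 0.68)/2 = 0.48. With 50% overall dropout split 80%/20% between the two halves, the end is 0.28×0.2 + 0.68×0.8 = 0.60. With a 70%/30% split it is 0.28×0.3 + 0.68×0.7 = 0.56.
- Selective rating alone, with liked messages rated 80% of the time and others 50%: 0.48×0.8/(0.48×0.8 + 0.52×0.5) = 0.384/0.644 = 0.60.

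**3. Same flat trend, different cause.** The no-preference cohort stays at 0.60 however the weights change. The favourite-topic cohort stays at 0.48 if the HRSA learns nothing.

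**4. What precision does capture.** For one fixed patient who likes one topic 90% of the time and the other four 30%:
- equal choice: (0.9 + 4×0.3)/5 = 0.42
- weights 0.6, 0.1, 0.1, 0.1, 0.1: 0.6×0.9 + 0.4×0.3 = 0.66
- always the favourite: 0.90

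The order is right. The difficulty is attribution, not direction.

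**5. Cost of an equal-choice reference by weighting.** Weighting each rated message by 0.2/w_k keeps an effective share of 1/Σ w_k(0.2/w_k)² = 1/(0.04 Σ 1/w_k):

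| Weights (assumed) | Σ 1/w | Effective share |
|---|---|---|
| 0.6, 0.1×4 | 41.67 | 60% |
| 0.8, 0.05×4 | 81.25 | 31% |
| 0.9, 0.025×4 | 161.11 | 16% |

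With 120×0.5 = 60 completers and 3×52/12 = 13 messages a month, about 780 are sent in month 12. If half are rated (assumption), 390 remain, worth about 234, 120 or 60 effective ratings, before allowing for clustering by patient.

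**The case against.** The strongest reply is that the declared outcomes are perceived quality and engagement, with quality meaning timely and relevant messages. On that reading a disliked message is an irrelevant recommendation and a fair miss, and hits over rated items is an ordinary precision measure. The article also compares with month 1 rather than reading a single level, itself uses the term acceptance rate, and warns in its Discussion against simplistic conclusions. Much of this stands: the metrics are legitimate measures of acceptance, and within a fixed cohort with real preferences they rise with better topic choice. It does not rescue the attribution. The Abstract, the text under Fig. 2 and Objective quality all tie the expected rise to the HRSA, and the Discussion's caution names no correction.

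Two stronger readings are tempting, and the documents do not support them.

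- **That precision says nothing about prediction.** Step 4 of the working shows otherwise.
- **That a disliked message from a low-weight topic was a correct prediction wrongly scored as a miss.** In the step 4 patient, 0.28 of the 0.34 not-liked share (82%) comes from topics weighted 0.1. But the vector is nowhere said to be a probability of liking. Weights that sum to 1 over five topics are relative, so a patient who likes everything could have 0.2 on each, and 0.1 is not a forecast of dislike. Nor does the article state outright that the topic is drawn at random from the vector, although "Just like the final decision of the message topic" in the sentence on timing makes that plausible.

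**Conclusion.** The point holds in a limited form. Precision_P and Precision_p&n are acceptance rates among rated messages. A level, a rise or a flat trend in them is not specific evidence of topic prediction, because general liking, dropout and selective rating can produce the same values. That the formulas omit topic and weight is plain from the text and needs no assumption. The sizes shown (0.60 with AUC about 0.50 or about 0.71; 0.48 to 0.60 with or without learning) rest on assumed like probabilities, weights and dropout patterns. They show what is possible, not what is expected.

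This does not invalidate the study. It limits what the planned metrics can conclude, and a cheap addition would let the study address its prediction question more directly.

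**What to change.** - **Keep both precision metrics and call them acceptance.** Word the expected rise as higher acceptance, not as evidence of accurate prediction.
- **Log the HRSA's full topic probability vector when each message is sent.** Do not rely on recomputing it later: overwritten ratings and editable interest answers may prevent recovery of the inputs as they stood.
- **Name the analysis of topic prediction.** Estimate within patient how the chance of a positive rating, and of a positive or neutral rating, varies with the weight of the sent topic. Account for clustering by patient and adjust for time. A mixed logistic model that separates within-patient from between-patient differences in weight would do.
- **Conditional secondary analysis.** If topics are confirmed to be drawn at random from the vector and every topic keeps a non-zero weight, also report precision minus its inverse-probability-weighted value under equal topic choice, with a confidence interval.

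The cost is one logged field and one model, with no change to what patients receive. The weighted contrast loses precision as the HRSA concentrates its weights (60% to 16% effective share for the vectors tried), so it should stay secondary. Neither analysis corrects for selective rating, and the report should say so.

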Attrition is a well-known problem in digital healthcare interventions [52]. It is important to increase appreciation and thus raise patient engagement, thereby keeping attrition to a minimum. This is especially relevant in m-HRS because the more user engagement with the system, the more the system learns about the user, and, consequently, the stronger the system becomes. Alkhaldi et al. explained the importance of user engagement in digital health interventions [53]. Although there are different definitions of engagement, the one used in this study was proposed by Alkhaldi et al. in the study “Users revisiting the digital intervention”. A high engagement in digital health interventions is also associated with better patient health outcomes [54, 55]. This is because engaged patients read more tailored motivational health messages and therefore receive more such prompts. This has a positive impact on their behavior change, such as quitting smoking, as some studies have already shown [56, 57]. However, the novelty effect may also influence their attrition. Consequently, it would be necessary to compare how patients’ opinions regarding the HRS messages evolve throughout the intervention.

In conclusion, the first goal of this study is to describe the patients’ perceived quality of the m-HRS. The second goal is to assess the patients’ level of engagement with the messages generated by the system. Identifying which system features and user characteristics determine differences in user engagement and quality perception may help improve the design of future m-HRS platforms.

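### Precision is compared only in months 1, 3, 6, 9 and 12, leaving about 55–56% of a completer's scheduled ratable messages outside the comparison; using every month would cost almost nothing

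*Protocol article*

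**What the plan says.** Outcomes makes perceived quality a primary outcome, and Objective quality makes precision one of its two objective measures. The time windows are part of the definition. Precision relates the "number of hits per message in the first month (baseline") to the "feedback per message in month 3, month 6, month 9, and month 12". A later sentence in the same section says that precision will be calculated at various times, but names no further months. On the feedback and interaction data, the section adds: "All this information is stored in the database of the m-HRS".

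Choosing the message topic says that patients are prompted to rate each message and that ratings feed the choice of the next one. Sending the messages excludes the preparation phase from rating and then gives the schedule: "Four messages on the day of quitting, and one message a day for the following week", followed by "Three messages a week after that, for one year". It also says that a completer "will receive a total of 150 messages from the m-HRS".

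On the aim, Background raises the novelty effect and concludes that "it would be necessary to compare how patients’ opinions regarding the HRS messages evolve throughout the intervention".

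**The concern.** The aim is a trajectory: how opinion of the messages changes through the year. The named comparison looks at five separate months. Month 2 falls between the baseline and the first follow-up window, and each later pair of windows is separated by two months. An early rise, a plateau or a passing dip can therefore be placed only roughly.

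The ratings from the other months already exist. Sample size caps recruitment at 120 with 50% dropout expected and no power analysis, and Limitations and generalizability names the capped sample as a weakness. In that setting, leaving recorded ratings out of a comparison on a primary outcome gives up information that further recruitment cannot replace.

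**Working it through.** **Inputs**
- Action phase (Sending the messages): 4 messages on quit day, then 1 a day for 7 days.
- Maintenance (same section): 3 a week, or 3/7 a day.
- Preparation messages cannot be rated, so they are outside the denominators of Equations 1 and 2.
- Windows (Objective quality): months 1, 3, 6, 9 and 12.
- Assumption: month k is counted from each patient's quit day, with a month of 365/12 = 30.42 days. The article does not state the clock.

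**The plan's own figures**
- 9000 messages: 120 × 0.5 × 150 = 9000. This reproduces.
- 150 messages per completer: 365 days from quit day give 4 + 7 + 357 × 3/7 = 164. A full 52 weeks of maintenance after the action phase gives 4 + 7 + 364 × 3/7 = 167. The stated 150 does not reproduce; the schedule yields 9–11% more. The two statements should be reconciled. The result below hardly depends on which is used.

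**Messages inside the windows (365 days)**
- Month 1: 4 + 7 + (30.42 − 8) × 3/7 = 20.6
- Each later window: 30.42 × 3/7 = 13.0; four of them, 52.1
- Inside: 20.6 + 52.1 = 72.7, and 72.7/164 = 44.4%
- Outside: 7 × 13.04 = 91.3, and 91.3/164 = 55.6%
- Month 2 alone: 13.0/164 = about 8%

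**Sensitivity of the share outside**

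| Variant | Inside / total | Outside |
|---|---|---|
| 365 days from quit day | 72.7 / 164 | 55.6% |
| Full 52-week maintenance | 72.7 / 167 | 56.4% |
| Rescaled to the stated 150 | 67.1 / 150 | 55.3% |
| 30-day months | 71.9 / 164 or 167 | 56.2% or 57.0% |
| 28-day months | 67.6 / 164 or 167 | 58.8% or 59.5% |

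**Front-loaded rating.** These are scheduled messages for a completer, while Equations 1 and 2 count only messages with feedback. As an illustration, a patient who rates everything and stops after month 3 has 20.6 + 13.0 + 13.0 = 46.7 rated messages (from unrounded values), of which only month 2 is outside: 13.04/46.7 = 28%. One who stops after month 6 has 20.6 + 5 × 13.04 = 85.8, with months 2, 4 and 5 outside: 39.1/85.8 = 46%. The article gives no monthly rating rates, so the true share cannot be calculated.

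**Within the baseline month.** The first eight days hold 4 + 7 = 11 of the 20.6 messages, or 53%. From day 9 the rate is constant.

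**The case against.** A month-1 baseline with quarterly follow-up is an ordinary prespecified grid. App features and clinical integration asks whether messages at the end of the pilot are preferred to those at the beginning, and months 1 and 12 answer that directly, with three points between. Five points would also show a sustained novelty decline. The general sentence in Objective quality does not exclude other months. All of this stands, and it is why the point is not an error. It does not remove the gain: the article commits to five months and no others, and the data for the rest are already held.

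Several stronger readings are tempting, but the article does not support them.
- A reader might infer that the other ratings are thrown away, or that month 2 goes unobserved. They are stored and train the algorithm. The messages also count in the individual read rate, which uses all messages sent, and time-to-read has no month restriction. They are absent only from the named precision comparison.
- A reader might infer that the first two months as a whole are message-dense and must hold most of the learning. Only the first eight days are dense, and these lie inside month 1. No learning curve is given, and Objective quality expects the highest acceptance in month 12, partly because more patients will have joined.
- A reader might infer that a patient who rates nothing in one window is lost at that point. Equations 1 and 2 are ratios of message counts and state no patient-level unit.
- A reader might take 56% as the share of ratings left out. It is a share of scheduled messages for a completer. If month k means study time with staggered entry, the split would not follow either.

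**Conclusion.** The point holds as an inexpensive improvement to a method the article does state. On a quit-day clock, about 55–56% of a completer's scheduled ratable messages lie outside the five windows (up to 59.5% with 28-day months), including all of month 2. More than half is outside under every month length and total tried. The share of actual ratings is unknown and falls if rating is front-loaded.

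The consequence is limited: a coarse view between windows, and a less precise trend than the stored data permit. The gain from using all months will be smaller than the message counts suggest, because ratings from one patient are likely to be correlated. The planned five-month comparison is not made invalid.

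**What to change.** Reword the definition of precision so that Equations 1 and 2 are computed for every month, or by message sequence number. Estimate the change over the year from all rated messages, allowing for repeated ratings within a patient (for example, a mixed logistic model or a logistic model with patient-clustered standard errors). Keep months 1, 3, 6, 9 and 12 as the displayed points, and state whether month k runs from quit day or in study time.

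Optionally, split month 1 so that the first eight days (11 messages), when the algorithm knows least about the patient, can be seen apart from the rest of the baseline month.

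The cost is a change of wording and a little more analysis. No new data are needed.
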